### Data quality, security and trial oversight

Reliability, validity and clinical relevance of outcomes are reported in online supplemental table 3. Processes to promote quality and security of collected data include general local training of site staff and research teams (Good Clinical Practice), and trial-specific training in the use of electronic forms and databases by LCTC. LCTC will request to see evidence of appropriate training and experience of all trial staff. Staff will be signed off as appropriately qualified by the CI. Electronic data capture provides several in-built validity and security checks (eg, data type, range and missingness checks in eCRFs, SleepSuite use/access restrictions). Some electronic and all hard copy data will be repeat checked (eg, eligibility, contact details). Data processing requiring more subjective judgement will be performed by minimum of two trained researchers on at least a subset of data (ie, manually assisted selection of actigraphy sleep period; thematic and content analysis of qualitative data).

Data will be processed and stored in accordance with GDPR under the UK Data Protection Act 2018. Central data monitoring will be performed by LCTC which will raise and resolve queries with site and research teams within the online system. The University of Liverpool is registered with the Information Commissioners Office. LCTC will receive trial participants’ HES identifiers for secure transfer to the Health Economic Team, who will access, securely store and dispose of HES data in accordance with the Bangor University and NHS Digital Data Sharing Framework Contract.

### Statistical methods

Statistical analyses of all but health economic and qualitative data will be performed by the trial statistician (LCTC) using SAS software, V.9.4 or later. Intention-to-treat will be the main analysis strategy for primary and secondary outcomes (see table 1 and table 5). Minimisation variables (including seizure frequency, AED and sleep medication details) will be adjusted for at baseline. Statistical significance will be set at the conventional two-sided 5% level; clinical relevance will be based on previous research (see online supplemental table 3). Point estimates with 95% two-sided CIs will be reported adjusted and unadjusted for covariates. No multiplicity adjustments will be made (only one primary clinical outcome, uncorrected secondary outcome analyses).

**Table 5 T5:** Analysis plan for outcome variables in CASTLE Sleep-E (further analyses details are reported in text)

Outcome type	Specific measurement variable	Hypothesis	Method of analysis
Primary			
Clinical	Children’s Sleep Habits Questionnaire^33^	Total score lower in intervention arm at 3 months	Linear mixed effect regression: Fixed effects: intervention (binary) Random effects: trial site (categorical) Covariates: Baseline score Use of sleep medication (binary)
Health economic	Cost* per quality-adjusted life year gained	Not applicable (health economic evaluation)	Cost-effectiveness (utility) analysis
Secondary			
Clinical	Children’s Sleep Habits Questionnaire^33^	Total score lower in intervention arm at 6 months	Linear mixed effect regression (as before)
Clinical	Seizure-free period	Time to first seizure (days) differs between trial arms at 3 and 6 months	Survival analyses Kaplan-Meier curves by trial arm Cox proportional hazards regression (if applicable) Covariates: Use of sleep medication (binary) Trial site (categorical)
Clinical	Time to 6-month seizure remission from randomisation (days)	Time to 6-month seizure remission (days) differs between trial arms at 6 months	Survival analyses (as before)
Clinical	Knowledge about Sleep in Childhood Actigraphy^53^ (2-week average): Total sleep time Sleep latency Sleep efficiency	Total score differs between trial arms at 3 months	Linear mixed-effects regression (as before)
Clinical	Hospital Anxiety and Depression Scale^49^ Insomnia Severity Index^43^	Total score lower in intervention arm at 3 and 6 months	Linear mixed-effects regression (as before)
Clinical	Sickness-related school absences	Total days differ between trial arms at 3 and 6 months	Poisson mixed-effects regression
Clinical	Health-Related Quality Of Life Measure for Children with Epilepsy^55^ WHO–Five Well-Being Index^50^	Total score differs between trial arms at 6 months	Linear mixed-effects regression (as before)
Clinical	SleepSuite^34^: animal task SleepSuite: bubble task Shape detection Emotion detection Gender detection SleepSuite: maze task	Executive function, reaction time and variability differ between trials arm at 3 months	Poisson/zero-inflated negative binomial regression (depending on presence of overdispersion) 2×2 multivariate repeated-measures analysis of variance Factors: Time (PM/AM)×intervention (pre/post) Fitted per detection task (shape, emotion, gender) Linear mixed-effects regression (as before)
Clinical	Strengths and Difficulties Questionnaire^51^ Parenting Self-Agency Measure^52^	Total score differs between trial arms at 3 and 6 months	Linear mixed-effects regression (as before)
Qualitative	Trial experience†	Not applicable (inductive)	Thematic analysis (interpretive, reflexive and conceptual analytical approach) Discrete sets: intervention/control, child/parent, engagement with intervention/lack thereof, decision-making types, responses/experiences Separately for child and parent, then jointly (dyad) Comparisons with selective objective data as emerging from analysis (eg, anxiety measures, actigraphy)

*Perspective: NHS and PSS perspective; alternative perspective: societal (indirect and direct non-medical costs).

†Source data for trial experience: qualitative interviews (parents and children individually and as dyad), activity booklets (children only).

CASTLE, Changing Agendas on Sleep, Treatment and Learning in Epilepsy; NHS, National Health Service; PSS, Personal Social Services.

Sensitivity analyses will be carried out if the amount of missing data is greater than 10%. Multiple imputation will be used to assess the robustness of the analysis to missing primary outcome data. The multiple imputation method will follow published guidelines.^35^ PROC MI in SAS (version 9.4 or later) will be used to generate 50 complete datasets. The imputation model will include all variables included in the primary outcome analysis model. The overall summary adjusted mean difference will be presented with 95% CIs, to assess the sensitivity of the primary analysis to missing data. All analyses will be reported in accordance with the Consolidated Standards of Reporting Trials Checklist^36^ and regardless of statistical significance.

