### Sample size

The target sample size (110 children with RE, 55 per trial arm) was calculated based on achieving 90% power to detect the minimal clinically important difference (MCID) in the primary clinical outcome (Children’s Sleep Habits Questionnaire (CSHQ)) at 3 months after randomisation, accounting for 10% expected attrition (non-parametric test with two-sided 5% significance level). MCID was defined based on an individual-focused anchor-based method,^31^ that is, ‘the smallest difference in outcome that patients perceive as beneficial and which mandates a change in patient management’.^32^ The MCID value was based on the estimated reduction in total CSHQ score required for children with epilepsy (M=48.25, SD=8.91)^7^ to fall at or below the diagnostic cut-off score of 41 for sleep disorders in paediatric populations.^33^

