### Treatment allocation

Participants will be allocated with a 1:1 ratio to either SC or SC+COSI based on a computer-generated adaptive restricted randomisation procedure that minimises differences between trial arms in variables likely to affect outcomes. Minimisation algorithm details are not published to avoid subversion of allocation sequence concealment, but include seizure frequency, AED and sleep medication details. The allocation concealment mechanism is an online, central randomisation service implemented and maintained by the Liverpool Clinical Trial Centre (LCTC). The service will be accessed within 4 weeks of participant enrolment (once consent and eligibility confirmed, participant ID issued, baseline dataset completed) by trained, authorised staff at trial sites. Randomisation will trigger allocation emails to the trial manager at LCTC and to the relevant trial site as well as enable COSI access for participants allocated to the intervention arm. Trial sites will notify the participant’s general practitioner of the treatment allocation by letter (electronic or hard copy, depending on preference).

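### The Statistical methods text promises adjustment for all minimisation variables, but the Table 5 models list only sleep medication among them, so the primary analysis is defined in two ways

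*Protocol article*

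**What the plan says.** Under Treatment allocation, the article withholds the details of the minimisation algorithm but says that they "include seizure frequency, AED and sleep medication details".

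Under Statistical methods, the text says: "Minimisation variables (including seizure frequency, AED and sleep medication details) will be adjusted for at baseline".

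Table 5, in the same section, specifies the primary CSHQ model with intervention as fixed effect, "Random effects: trial site (categorical"), and "Covariates: Baseline score Use of sleep medication (binary"). The other linear mixed models, including CSHQ at 6 months, are given as the same model by back-reference. The time-to-first-seizure row has its own list, "Covariates: Use of sleep medication (binary) Trial site (categorical"), and the 6-month-remission row refers back to it.

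The caption of Table 5 adds "further analyses details are reported in text". The paragraph on missing data says: "The imputation model will include all variables included in the primary outcome analysis model".

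**The concern.** Neither seizure frequency nor AED appears in any covariate list in Table 5, although both are named as minimisation variables and the text says that those are adjusted for. A statistician who follows the text and one who follows the table would fit different primary models and report different estimates, intervals and p-values. Only one of these can be the pre-specified analysis. In an open-label trial with a parent-reported primary outcome, the covariate set should not be open to choice once data are available. The multiple imputation model is defined by reference to the primary model, so it has the same gap.

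The second issue is statistical. Minimisation balances the factors across arms and so removes their contribution to the variability of the treatment difference. A model that omits them leaves their contribution in the residual variance. If they are prognostic, the reported standard error then exceeds the true one. For time to first seizure, omitting baseline seizure frequency, an obvious candidate predictor, can also pull the hazard ratio towards 1, because the hazard ratio is non-collapsible.

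**Working it through.** **1. The two specifications side by side**

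| Term | Text | Table 5, primary and 'as before' linear models | Table 5, Cox models |
|---|---|---|---|
| Sleep medication | yes | yes | yes |
| Seizure frequency | yes | not listed | not listed |
| AED | yes | not listed | not listed |
| Baseline score | not mentioned | yes | not applicable |
| Site | not mentioned | random effect | covariate |

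This mismatch needs no assumption.

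**2. The plan's own figures**

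The Sample size section gives 110 children (55 per arm), 90% power, two-sided 5%, a non-parametric test, 10% attrition, SD 8.91, and a target derived from a mean of 48.25 and a cut-off of 41.

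- Implied difference: 48.25 − 41 = 7.25 points, or 7.25/8.91 = 0.81 SD.
- n per arm = 2 × [8.91 × (1.960 + 1.2816)/7.25]² = 31.7, so 32. Dividing by a Wilcoxon relative efficiency of 3/π = 0.955 gives 34; 34/0.9 rounds up to 38 per arm, or 76 in total.

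The stated 110 is therefore not reproduced from these inputs. That is a separate matter and does not bear on the covariate lists. What matters here is that the section mentions no covariates, so the 90% cannot be read as the power of a model that already includes seizure frequency and AED. Analysed number: 110 × 0.9 = 99, or 49.5 per arm.

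**3. Effect of omission in the linear model**

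Let R² be the share of residual 3-month CSHQ variance (given baseline score and sleep medication) explained by seizure frequency and AED. The article gives no value, so 0 to 20% is assumed. With the factors fully balanced:

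- SE ratio, omitted to adjusted: 1/√(1 − R²)
- Real type I error when omitted: 2[1 − Φ(1.96/√(1 − R²))]
- Power when omitted, if a model without the factors has a nominal 90%: Φ(1.2816/√(1 − R²))
- Power when adjusted, on the same basis: Φ(3.2415/√(1 − R²) − 1.96)

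| R² | SE too large by | Type I, omitted | Power, omitted | Power, adjusted | Gain forgone |
|---|---|---|---|---|---|
| 0 | 0% | 5.0% | 90.0% | 90.0% | 0 |
| 10% | 5.4% | 3.9% | 91.2% | 92.7% | 1.6 points |
| 20% | 11.8% | 2.8% | 92.4% | 95.2% | 2.8 points |

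(Gains are taken from unrounded powers.)

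**4. Simulation check**

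4000 trials per scenario, 99 analysed, minimisation on three binary factors with a 0.8 biased coin, assumed baseline correlation 0.5, site effect left out:

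| R² | SE too large by | Type I, omitted / adjusted | Power at 5 points, omitted / adjusted |
|---|---|---|---|
| 0 | 0% | 5.1% / 5.0% | 88.5% / 88.3% |
| 10% | 5% | 4.5% / 5.7% | 90.0% / 91.1% |
| 20% | 12% | 2.8% / 4.9% | 91.3% / 94.5% |

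Simulation error on the type I figures is about 0.3 points. The SE ratios agree with the formula. Power under omission rises with R²; it rises more under adjustment.

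**5. At the implied 7.25 points**

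Without baseline adjustment, 7.25/(8.91 × √(2/49.5)) = 4.048. Power, omitted against adjusted, is 98.6% against 98.9% at R² = 10%, and 99.0% against 99.5% at R² = 20%. With the assumed baseline correlation of 0.5, the simulation gives more than 99% in both models.

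**6. Time to first seizure**

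The article states neither an event rate nor how strongly seizure frequency predicts seizures, so the attenuation of the hazard ratio can be given a direction but not a size.

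**The case against.** The best defence is that the table is a summary. Its caption sends the reader to the text, and the text supplies the missing factors, so nothing is omitted. That reading is possible, and for this reason the documents do not establish that the factors will be left out. It does not settle the matter, because Table 5 gives an explicit list that contains one named minimisation variable and not the other two, and a pointer to further detail does not say that the text overrides that list.

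It could also be said that the adjustment sentence describes the minimisation itself. Its place in Statistical methods, shortly before the promise of estimates with and without covariate adjustment, makes model adjustment the natural reading.

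Confidentiality of the algorithm is a fair reason not to publish every factor and its coding. It does not explain leaving out two factors that the article names twice.

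A reader might infer that following Table 5 pushes power below 90%, for example to 88% or 85%. Those values come from treating 90% as the power of the fully adjusted model, which the Sample size section does not support. A reader might also infer a bias or a false-positive risk in the primary result. In the linear model, omission of balanced factors produces neither; the test errs on the cautious side.

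The sickness-absence Poisson row lists no covariates at all. That is condensation in an article, not a contradiction.

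**Conclusion.** The contradiction stands on the article's own words and affects the primary analysis, the linear models that refer back to it, the Cox models and the imputation model. It should be resolved before analysis.

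The statistical consequence is conditional and modest. It arises only if Table 5 governs and if seizure frequency and AED predict 3-month CSHQ beyond its baseline value. For an assumed R² of 0 to 20%, standard errors are 0 to 12% too large, the real type I error lies between about 5% and 2.8%, and roughly 0 to 3 points of attainable power are forgone. At the 7.25 points implied by the Sample size section, the loss is half a point or less. If the factors are not prognostic, there is no loss. For time to first seizure, attenuation towards 1 is to be expected if baseline seizure frequency is prognostic, but its amount cannot be fixed from the article.

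**What to change.** Add seizure frequency and AED to the Table 5 covariates for the primary model, the linear models that refer back to it, and the Cox models, so that table and text agree. Any further minimisation factor, and the coding used in allocation, can go in the SAP if the algorithm must stay confidential. Keep site as Table 5 already has it: random in the linear models, a covariate in the Cox models. State that the estimate adjusted for this list is the primary result and that the unadjusted one is supportive. The imputation model then follows without further change. If the shorter list is in fact intended, correct the text instead and give the reason for leaving out two balancing factors.

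The cost is a change of wording and a few degrees of freedom with about 99 analysed children.

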### Trial setting and eligibility criteria

Participants will be identified by staff in National Health Service (NHS) outpatient general paediatric and paediatric epilepsy clinics in the UK (predominantly urban setting). Eligibility criteria for participants are reported in online supplemental table 1, field 14 of the WHO Trial Registration Data Set (V.1.3.1). In the UK, a clinical RE diagnosis is based on electroclinical criteria defined by the International League Against Epilepsy (https://www.ilae.org/). Semiology and electroencephalogram (EEG) need to be judged as concordant by a consultant neurophysiologist. Neuroimaging does not form part of UK SC for RE. Eligibility criteria for trial sites include a capacity and capability assessment as advised for NHS site set-up by the UK Health Research Authority (HRA). The expected number of trial sites is 40 (England: 34, Scotland: 4, Wales: 1, Northern Ireland: 1). A list of trial sites can be obtained from the trial manager (see online supplemental table 1).

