### Recruitment, stopping guidelines and interim analyses

An Independent Data and Safety Monitoring Committee will monitor recruitment and make recommendations to the Trial Steering Committee (TSC) concerning trial continuation, adjustments of recruitment methods and follow-up optimisation (see online supplemental table 2). A traffic light approach will determine trial continuation: (1) green: continue if at least 30 trial sites have opened and 22 participants have been randomised by end of month 6; (2) amber: implement additional recruitment strategies if 15–21 participants have been randomised by end of month 6; (3) red: if recruitment is <15 participants by end of month 6, then stopping the trial early will be discussed with the TSC. Formal interim analyses of the accumulating data will not be performed.

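### Entering about 40 sites as a categorical covariate in the Cox models, with 110 children, more than doubles the type I error and exaggerates a real hazard ratio

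*Protocol article*

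**What the plan says.** In Table 5 (Statistical methods), the row for the seizure-free period gives Kaplan-Meier curves by arm and then "Cox proportional hazards regression (if applicable) Covariates: Use of sleep medication (binary) Trial site (categorical". The row for time to 6-month seizure remission repeats this: "Survival analyses (as before".

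The primary outcome row of the same table handles site differently: "Random effects: trial site (categorical". The other linear models follow that row.

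Two further statements set the scale. Trial setting and eligibility criteria: "The expected number of trial sites is 40 (England: 34, Scotland: 4, Wales: 1, Northern Ireland: 1". Sample size: "The target sample size (110 children with RE, 55 per trial arm". Significance is judged at a two-sided 5% level, with no multiplicity adjustment. The article gives no seizure event rate and no rule for merging small sites.

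**The concern.** Table 5 keeps random effects and covariates apart, so a categorical site term listed as a Cox covariate means one indicator per site. With two or three children per site, the number of nuisance parameters grows almost as fast as the sample. The usual large-sample theory then fails in three ways:

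- The treatment log hazard ratio is pushed away from zero when there is a real effect.
- Its model-based standard error is too small.
- A site with no event has no finite site estimate, so the fit produces convergence warnings.

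Seizure freedom is an important clinical secondary outcome, tested at an uncorrected 5%. A false positive, or an overstated effect with too narrow an interval, would pass straight into the report.

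**Working it through.** **Inputs from the protocol article.** 110 children, 1:1; 40 expected sites; 6 months' follow-up; two-sided 5%. The article states no event number, hazard ratio or power for the seizure outcomes, so there is no figure of its own to reproduce. The benchmark is the nominal 5%.

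**Assumptions, varied.** Control-arm seizure probability 30, 50, 70 or 90%; site log-hazard SD 0 to 0.5; 20% on sleep medication; true hazard ratio 1 or 0.60; sites equal or unequal in size.

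**Step 1: density.** Children per site: 110 / 40 = 2.75. Site parameters: 40 − 1 = 39. Under the null, events are 33, 55, 77 and 99 at the four event shares. Events per site parameter are 33/39 = 0.85, 55/39 = 1.41, 77/39 = 1.97 and 99/39 = 2.54.

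**Step 2: 40 equally filled sites** (two or three children each, site SD 0, 1,500 trials per scenario, Monte Carlo SE about 0.01). The Cox model has treatment, sleep medication and site indicators. The comparators omit site or stratify by it.

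Type I error, true HR 1:

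| Event share | Site indicators, Wald | Site indicators, likelihood ratio | Site omitted | Stratified by site |
|---|---|---|---|---|
| 30% | 0.169 | 0.181 | 0.051 | 0.048 |
| 50% | 0.146 | 0.151 | 0.047 | 0.047 |
| 70% | 0.159 | 0.161 | 0.055 | 0.057 |
| 90% | 0.136 | 0.137 | 0.055 | 0.050 |

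This is 0.136/0.05 = 2.7 to 0.181/0.05 = 3.6 times nominal. The likelihood-ratio test is no remedy.

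Median fitted HR, true HR 0.60:

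| Event share | Site indicators | Site omitted | Stratified by site |
|---|---|---|---|
| 30% | 0.468 | 0.597 | 0.583 |
| 50% | 0.475 | 0.596 | 0.593 |
| 70% | 0.463 | 0.597 | 0.591 |
| 90% | 0.471 | 0.599 | 0.591 |

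Under HR 1 the estimates stay centred near 1 (medians 0.96 to 1.02 over all 40-site scenarios). The bias arises only when there is an effect.

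**Step 3: fewer or uneven sites** (unequal site sizes).

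| Sites opened / with any child | Type I error, Wald | Median HR for true 0.60 |
|---|---|---|
| 40 / about 32 (30–90% events, site SD 0.5) | 0.095–0.109 | 0.52–0.53 |
| 30 / 25 (60% events, site SD 0.3) | 0.098 | 0.54 |
| 20 / 18 (60% events, site SD 0.3) | 0.093 | 0.56 |

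**Step 4: separate simulations.**

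- 600 trials, 40 equally likely sites, site SD 0.3: type I error 0.118, 0.120 and 0.113 at 30, 50 and 70% events, against 0.042 without site at 50%. For a true HR of 0.60 the mean log HR was −0.682 against ln 0.60 = −0.511, so exp(−0.682) = 0.51. Some site had no event in every run.
- 500 trials: 0.144 to 0.156 at 30 to 70% events, and 0.086 with uneven recruitment, against 0.058 to 0.064 without site. On average 11 to 40% of enrolling sites had no event.
- 400 trials: 0.12 with equally likely sites and 0.115 to 0.118 with about 32 filled, against 0.045 to 0.055 without site. Median HR 0.52 for a true 0.60.

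**Step 5: does the standard error explain it?** The empirical SD of the log HR was 0.49 against a mean model SE of 0.37. A nominal 5% Wald test then cuts at 1.96 × 0.37/0.49 = 1.48 true standard deviations, and 2 × [1 − Φ(1.48)] = 0.139, in line with the simulated rates.

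**Step 6: the alternatives.** A Gaussian shared frailty (500 trials per scenario) gave type I error 0.062 to 0.070 with equal sites and 0.046 with unequal sites, median HR 0.58 for a true 0.60, and power about 0.39. Site indicators gave 0.41 in that run, a figure inflated by their excess rejections. Stratifying by site keeps the error nominal but costs power: 0.22 against 0.39 with site omitted (40 equal sites, 50% events, HR 0.60).

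**The case against.** The size depends on how many sites enrol and how evenly, and the article gives only an expected number of sites. With uneven recruitment and about 32 sites filled, the error was 0.086 to 0.118 across the simulations, which is about double. With 18 to 25 sites it was slightly under double. This stands and belongs in the statement of size. It does not rescue the model: the plan itself expects 40 sites, and its continuation rule asks that "at least 30 trial sites have opened and 22 participants have been randomised by end of month 6".

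The Statistical methods text also promises estimates without covariate adjustment beside the adjusted ones. A distorted adjusted hazard ratio would therefore be visible, but the adjusted result would still be wrong.

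The quantitative analysts are blinded, and sites without events can be seen in pooled data. A change of model could be made before unblinding, so a late ad hoc change is a risk and not a certainty.

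These are secondary outcomes. The primary sleep score model has a random site effect and is unaffected. The figures apply to time to first seizure; the remission outcome was not simulated, although it inherits the same site term.

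Finally, a small-site rule might sit in the SAP. The point here, however, is a model that Table 5 states, not a missing detail.

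**Conclusion.** The concern holds. At the planned 40 sites, fixed site effects raise the Wald type I error of the adjusted time-to-first-seizure analysis from 5% to between 11 and 17%. The error is about double when recruitment is uneven and close to double even with 18 to 25 enrolling sites. A true hazard ratio of 0.60 is typically reported as 0.46 to 0.52 with 40 equal or equally likely sites, and as 0.52 to 0.56 with 18 to 32 filled. Under the null the hazard ratio itself is not biased.

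The inflation appeared at every event share from 30 to 90% and with site SDs from 0 to 0.5, so it does not turn on one assumed value. It does rest on reading the Cox site covariate as fixed effects, which is what the contrast with the linear models in the same table implies.

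**What to change.** In Table 5, take site out of the covariate list in both Cox rows and enter it as a shared frailty (random effect), matching the linear models. Alternatively, leave site out of the Cox models. State the choice in the SAP before unblinding. Stratification by site is valid but is the weaker option here because of its loss of power.

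In the same edit, bring the Cox covariates into line with the Statistical methods text, which says the minimisation variables, including seizure frequency and AED details, will be adjusted for. The Cox row names only sleep medication. Removing up to 39 site terms makes room for these.

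The cost is wording in Table 5 and the SAP and one RANDOM statement in the planned SAS software. Data collection and sample size do not change. The frailty variance may be estimated as zero, in which case the model reduces to one without site, which performed acceptably in the simulations. The change corrects the site term only; the remission outcome needs its own check, since these simulations do not cover it.
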